## Abstract

**Background:**

The insertion of a Totally Implantable Access Port (TIAP) is a routinely employed technique in patients who need a safe and permanent venous access. The number of TIAP implantations is increasing constantly mainly due to advanced treatment options for malignant diseases. Therefore it is important to identify the implantation technique which has the optimal benefit/risk ratio for the patient.

**Study design:**

A single-centre, randomized, controlled superiority trial to compare two different TIAP implantation techniques. Sample size: 160 patients will be included and randomized intra-operatively. Eligibility criteria: Age equal or older than 18 years, patients scheduled for primary elective implantation of a TIAP in local anaesthesia and a signed informed consent. Primary endpoint: Primary success rate of the randomized technique. Intervention: Venae Sectio in combination with the Seldinger Technique (guide wire and a peel away sheath) will be used to place a TIAP. Reference treatment: Conventional Venae Sectio will be used with a direct insertion of the TIAP without guide wire or peel away sheath. Duration of study: Approximately 20 months.

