#### Patients needed

If the real success rate difference is minimum 15% (80% vs. 95%) then there is a 80% chance that a trial involving 160 patients could detect a significant difference at a level of 5%.

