### Study organization

All patients scheduled for a primary port-catheter-system implantation procedure in the Outpatient-Clinic of the Department of Surgery, University Hospital of Heidelberg, will be referred to the Centre for Clinical Studies in Surgery (KSC) and screened by members of the KSC [4]. The result of the screening will be recorded in the screening-log.

Approximately 500 patients per year undergo a port-catheter-system implantation at the Outpatient-Clinic of the Department of Surgery, University of Heidelberg. The estimated time frame to randomize 180 patients is approximately 18 months.

The independent data management and monitoring will be done by the Coordination Centre for Clinical Trials (KKS) Heidelberg.

The principal investigator has the right to terminate the trial and to remove all trial material from the trial centre at any time in consultation with the Clinical Study Team Leader and the Biometrician. Reasons that may require a termination of the trial include the following:

• The incidence or severity of adverse events in this trial indicates a potential health hazard caused by the study treatment

• It appears that patient's enrolment is unsatisfactory with respect to quality and/or quantity or data recording is severely inaccurate and/or incomplete

• External evidence that makes it necessary to terminate the trial

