### Financial support

One half of the costs for this study will be financed by the Surgical Foundation Heidelberg (Stiftung Chirurgie Heidelberg), the other half will be sponsored by Fresenius Kabi AG ^©^. This concept of a half-half financial support will help to guarantee the independency of the final study analysis and its results from commercial interests.

**Table 1 T1:** Flowchart according to CONSORT

	To be assessed for eligibility (n = 280)	
		Total to be excluded (n = 100) refusal to participate (n = 40) not meeting inclusion criteria prior to surgery (n = 20) no cephalic vein present (n = 20) other reasons (n = 20)
	To be randomized (n = 180)	
Experimental Group		Control Group
To be allocated to intervention (n = 90) receive allocated intervention (n = 80) don't receive allocated intervention (n = 10)		To be allocated to intervention (n = 90) receive allocated intervention (n = 80) do not receive allocated intervention (n = 10)
To be analyzed (n = 80)		To be analyzed (n = 80)

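### The abstract randomises 160 patients while the organisation section and Table 1 randomise 180, and the power statement does not say which number it refers to

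*Protocol article*

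**What the plan says.** - **Abstract, Study design:** "160 patients will be included and randomized intra-operatively".
- **Patients needed:** for success rates of 80% and 95%, power of 80% is claimed on the footing that "a trial involving 160 patients could detect a significant difference at a level of 5"%. The word used is involving, not randomising or analysing, and no allowance for loss or non-receipt is given.
- **Study organization:** "The estimated time frame to randomize 180 patients is approximately 18 months".
- **Table 1:** "To be randomized (n = 180"), then in each arm "To be allocated to intervention (n = 90"). In the experimental arm "don't receive allocated intervention (n = 10"), with the same number in the control arm. That leaves 80 per arm who receive the technique and 80 per arm to be analysed.
- **Analysis:** the primary endpoint is compared by chi-square test in all included patients by intention to treat, with a second, per-protocol analysis.

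**The concern.** The abstract, the Study organization section and Table 1 all give the number to be randomised. The abstract says 160 and the other two say 180. No sentence in the article reconciles them.

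The number randomised fixes when recruitment ends, and readers will check it against the final report. The power claim also depends on it. If 160 is the number randomised, the sample-size section has no room for the 20 patients whom Table 1 expects not to be treated as allocated. If 160 is the number left after removing those 20, the power claim describes a set restricted to patients treated as allocated, whereas the Analysis section makes intention to treat the main comparison.

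**Working it through.** **Inputs.** Success 80% versus 95%, 5% level and 80% power (Patients needed). 160 randomised (Abstract). 180 randomised, 90 per arm, 10 per arm not receiving the allocated technique, 80 per arm analysed (Table 1). Chi-square test (Analysis). The document does not state sidedness, so two-sided is assumed.

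**1. The plan's own figure.** With n per arm, p1 = 0.80, p2 = 0.95 and mean rate 0.875, the normal approximation is

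power = Φ{ [0.15·√n − 1.96·√(2·0.875·0.125)] / √(0.80·0.20 + 0.95·0.05) } = Φ{ [0.15·√n − 0.917] / 0.4555 }.

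- Required n for 80% power: (0.917 + 0.842·0.4555)² / 0.15² = 75.1, so 76 per arm (152 in total). With continuity correction it is 88 per arm (176 in total).
- At n = 80: Φ{(1.342 − 0.917)/0.4555} = 82.5%. Exact binomial enumeration gives 84.9% for the uncorrected chi-square test, 79.3% for Fisher's exact test and 76.8% for the continuity-corrected test.

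The stated 80% with 160 patients is therefore reasonable if all 160 are analysed and the planning rates apply to all of them. The sample size itself is not the fault.

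**2. Link between the two numbers.** Non-receipt in Table 1 is 20/180 = 11.1%, and 160 / (1 − 20/180) = 180 exactly. So 180 is 160 inflated for non-receipt.

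**3. All 180 analysed, with 80% versus 95% applying to everyone.** At n = 90: Φ{(1.423 − 0.917)/0.4555} = 86.7%. Exact chi-square gives 89.0%.

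**4. All 180 analysed, with 10 of 90 per arm not treated as allocated.** Arm rate = (80/90)·(planning rate) + (10/90)·(rate in those not treated as allocated). The document does not give that last rate, so four assumptions are shown.

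| Assumed success in the 10 per arm | Arm rates | Power, normal approximation | Power, exact chi-square |
|---|---|---|---|
| All count as failures | 71.1% vs 84.4% | 58% | 58% |
| Rate of the other arm | 81.7% vs 93.3% | 66% | 68% |
| 80% in both arms | 80.0% vs 93.3% | 75% | 77% |
| 95% in both arms | 81.7% vs 95.0% | 80% | 83% |

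The range is about 58% to 83%.

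**5. Only 160 randomised, with Table 1's loss applied.** 160·(80/90) = 142 analysed, or 71 per arm. Normal approximation: Φ{(1.264 − 0.917)/0.4555} = 77.7%. Exact chi-square: 80.4%.

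**The case against.** Table 1 largely explains the two figures: 180 are randomised, 20 are not treated as allocated and 160 are analysed. The sample-size section speaks only of a trial involving 160, which does not contradict 180. The two operational places agree on 180. On this view one abstract sentence is wrong and the rest is a missing label.

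Much of that stands. It shows that there were not two independent sample-size calculations, and it lowers the severity. It does not remove the point. The abstract still calls 160 the number randomised, the allowance is still unstated where the power is claimed, and the explanation works only if 20 randomised patients leave the analysis, which conflicts with intention to treat.

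A reader might infer two stronger things that the document does not support.

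- *That the trial could test at 160 and again at 180, inflating the type I error.* No analysis at both numbers is planned. The termination reasons listed under Study organization are adverse events, poor enrolment or data quality, and external evidence; efficacy is not among them. Biometry and data management sit with an independent coordination centre.
- *That stopping at 160 randomised, with 142 analysed, clearly misses 80% power.* The normal approximation gives 77.7%, but exact enumeration of the uncorrected chi-square test gives 80.4%. The shortfall depends on the method of calculation.

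It is also fair to say that the wide power range in step 4 comes mainly from keeping patients not treated as allocated in the comparison, not from the gap between 160 and 180. It matters here only because the power statement has to be attached to a defined set.

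**Conclusion.** Wrong as written. The article gives two values for the number to be randomised, 20 patients apart (12.5% of 160), and its power statement is not tied to a defined analysis set. The likely intention is 180 randomised and 160 treated as allocated. On that reading the abstract is wrong, and the 80 per arm analysed in Table 1 disagrees with the Analysis section.

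For the intention-to-treat set of 180, power is about 87% to 89% if the planning rates hold for everyone. It is about 58% to 83% with 11% non-receipt. The second range rests on assumed outcomes for those patients, and both rest on a two-sided 5% test. The point should be corrected, but it does not undermine the trial: 160 patients is a sound number at the stated rates, and recruitment of 180 is already planned.

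**What to change.** 1. Give one number to be randomised, 180 (90 per arm), in the abstract, the sample-size section, the Study organization section and Table 1.
2. Label 160 as the number expected to receive the allocated technique, and state the allowance (20 of 180, 11.1%) in the sample-size section.
3. Have Table 1 show 90 per arm analysed for the intention-to-treat comparison, with 80 per arm shown separately as the number expected to receive the allocated technique.
4. Restate power for the intention-to-treat set, and say what success rate is assumed for patients not treated as allocated.
5. State that recruitment ends at the fixed number, subject to the termination reasons already listed under Study organization.

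The cost is a few sentences, one row of Table 1 and one power calculation. No extra patients are needed beyond the 180 already in the time frame and flow chart.

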**Organisation/Responsibility:**

The trial will be conducted in compliance with the protocol and in accordance with the moral, ethical, and scientific principles governing clinical research as set out in the Declaration of Helsinki (1989) and Good Clinical Practice (GCP). The trial will also be carried out in keeping with local and regulatory requirements. The Klinisches Studienzentrum Chirurgie (KSC) – Centre of Clinical Trials in Surgery at the Department of Surgery, University Hospital Heidelberg is responsible for planning and conduction of the trial. Documentation of patient's data will be accomplished via electronical Case Report Files (eCRF) with MACRO^®^-Software by the KSC. Randomization, data management, monitoring and biometry are provided by the independent Koordinierungszentrum für Klinische Studien (KKS) – Coordination Centre for Clinical Trails at the University of Heidelberg.

## Background

### Totally Implantable Access Ports (TIAP)

Insertion of a Totally Implantable Access Port (TIAP) is a routinely employed technique in patients who need a save and permanent venous access for e.g. chemotherapy and/or parenteral nutrition[1]. This system needs no external dressing, allows the patient normal physical activity, is probably less prone to infectious complications and will minimize the occlusion rate of the catheter compared to non-totally implantable catheters[1]. TIAPs are being extensively used world-wide and an increase of port placement can be expected with the broader introduction of innovative therapies in oncology such as the Capri Protocol in pancreatic cancer[2].

### Implantation techniques

Until today, two alternative approaches to access the central venous system are in use: Blind puncture of a central vein and introduction of a catheter using the Seldinger Technique or implantation of the TIAP through a surgically dissected vein (e.g. Venae Sectio of the cephalic vein; Fig. 1, 2). Both procedures are currently performed by surgeons as well as interventional radiologists and have a certain risk of complications with respect to the applied technique (pneumothorax, hematothorax, "pinch off" phenomena i.e. kinking of the catheter, nerve palsy, thoracic duct injury)[1,3].

**Figure 1 F1:**
[figure not shown]
Venae Sectio - Incision of V. cephalica.

**Figure 2 F2:**
[figure not shown]
Venae Sectio - Insertion of the catheter.

### Modified Seldinger Technique (combination of Venae Sectio and Seldinger Technique)

The modified Seldinger Technique is a combination of Venae Sectio and Seldinger Technique using a guide wire and a peel away sheath in the surgically dissected cephalic vein. We believe that the usage of the guide wire and peel away sheath allowes introducting the catheter even in a small cephalic vein and it offers the possiblity to insert the catheter beyond obstacles and narrow curves. The advantage of this technique should be the avoidance of the blind puncture of a central vein (e.g. subclavian vein) and therefore a lower risk of severe complications like pneumothorax, haematothorax and nerve palsy and the possibility to insert the catheter beyond obstacles or narrow curves of the cephalic vein (Fig. 3, 4, 5, 6, 7).

**Figure 3 F3:**
[figure not shown]
Venae Sectio + Seldinger - Insertion of the guide wire.

**Figure 4 F4:**
[figure not shown]
Venae Sectio + Seldinger - Insertion of the dilatator and peel away sheath over the guide wire.

**Figure 5 F5:**
[figure not shown]
Venae Sectio + Seldinger - Insertion of the dilatator and peel away sheath over the guide wire.

**Figure 6 F6:**
[figure not shown]
Venae Sectio + Seldinger - Dilatator removed and catheter introduced over the guide wire.

**Figure 7 F7:**
[figure not shown]
Venae Sectio + Seldinger - Removing of the peel away sheath.

### Medical problem

Correct placement of the TIAP in the superior Vena Cava is mandatory for optimal and save usage of the central venous access. The success rate of TIAP implantation via the conventional approach by transsection of the cephalic vein (Venae Sectio) ranges between 70 to 94%[3]. A multivariate analysis of 400 patients at the Department of Surgery, Universityhospital of Heidelberg, who underwent a primary port-catheter-system engrafting, showed a success rate of the conventional approach of 80%[3]. One of the major causes for failure was an undersized cephalic vein or an obstacle on the way to the superior Vena Cava[3]. Furthermore this study showed that the secondary approach to blind puncture the subclavian vein with Seldinger Technique achieves an overall success rate of 98% but was also characterized by a number of severe complications causally related to indirect puncture, like a pneumo- or hematothorax[1]. In almost all interventional series using the Seldinger technique, pneumothorax as a complication occurred (0 to 3.2%)[3]. In contrast a literature search was not able to identify pneumothorax or nerve palsy after implantation of a TIAP via Venae Section.

## Study design

### Aim of study

The objective of this trial is to compare the success and complication rates of two different implantation techniques for TIAP: Venae Sectio of the cephalic vein and direct insertion of the port catheter versus Venae Sectio and insertion of the port catheter with a guide wire and peel away sheath (modified Seldinger Technique).

### Number of patients needed

Two main factors determine the number of patients needed in a trial. These are the estimated event rate, and the size of the treatment effect.

#### Estimated event rate

The multivariate analysis of 400 patients at our Department who underwent a TIAP implantation showed a success rate of the conventional approach (Venae sectio with insertion of the catheter without a guide wire) of 80%.

#### Size of treatment effect that should be detectable

A modification of the conventional approach as described above must have by surgical decision an expected success proportion of 0.95[1], if surgical practice should be changed.

#### Patients needed

If the real success rate difference is minimum 15% (80% vs. 95%) then there is a 80% chance that a trial involving 160 patients could detect a significant difference at a level of 5%.

### Eligibility

#### Inclusion criteria

• Benign and malignant diseases which demand a safe and permanent venous access, e.g. for chemotherapy and/or parenteral nutrition

• Age equal or greater than 18 years

• Patients scheduled for primary elective implantation of a port-catheter-system in local anaesthesia

• Informed consent

#### Exclusion criteria

• Participation in another intervention-trial with interference of intervention and outcome of this study

• Lack of compliance

• Impaired mental state or language problems (Patient is not able to read german texts)

#### Subject withdrawal criteria

• Randomization will be carried out after preparation of the cephalic vein. If no vein is to exhibit the subject will be removed from the trial and the pre-rand drop-out is to record in the CRF

• At their own request or at request of the legal representative

• If, in the investigator's opinion, continuation of the trial would be detrimental to the subject's well-being

### Consent

Patients who are scheduled for port-catheter-system implantation will have a pre-treatment visit to give the informed consent. During this visit the patient will be screened and informed about the PORTAS trial. In this conversation with the patient the study procedure, risks, benefits and data management will be clarified in detail.

### Randomization and procedures for minimizing bias

#### Minimizing systematic bias

In order to achieve comparable groups for known and unknown risk factors a block randomization will be performed by the randomization software RITA^®^. A sufficient number of patients will be recruited according to the sample seize calculation in order to prevent random error. Patients will get randomized intra operatively after identification of the cephalic vein in order to minimize post randomization drop outs.

#### Minimizing treatment bias

All physicians who participate in this trial will be trained and updated every 3 month to guarantee comparable treatment of patients. Special manuals will be used in operation theatre to reduce random errors. In addition the learning curves of the participating surgeons will be assessed.

#### Minimizing measurement bias

An independent nurse will document and monitor the procedure in the operating theatre. Blinding is not possible and necessary due to the research question.

### Study treatment

All patients will be positioned on the table in a five degree reverse Trendelenburg's position. The neck, chest and shoulders of the patients will be prepared and draped in the customary sterile manner. Antibiotic prophylaxis is only given in patients of risk for endocarditis according to the local standards. Local anaesthesia will be infiltrated in sterile fashion into skin and subcutaneous layer and skin incision will be done 4 cm infer laterally parallel to the clavicle in the deltoid-pectoral region. The cephalic vein is to exhibit. After exhibition of the cephalic vein the randomization will be performed on a Laptop computer system with the RITA^® ^randomization tool.

According to the allocation the procedure will be continued.

#### Intervention-group 1

The cephalic vein will be legated distally and encircled cranially with a 3-0 reabsorbable suture. The vein will be cross-sected ventrally and the catheter flushed with heparinized saline, introduced. Correct positioning will be controlled via fluoroscopy (tip of catheter just at aditus of right atrium) (Fig. 1, 2).

#### Intervention-group 2

The cephalic vein will be ligated distally and encircled cranially with a 3-0 reabsorb able suture. The vein will be cross-sected ventrally and a guide wire will be placed under fluoroscopy to the junction of the superior vena cava and right atrium. After insertion and correct positioning of the wire, a vein dilator and sheath will be passed over the guide wire. The guide wire and dilator will be removed, and the catheter will be introduced through the peel-away sheath. After insertion the peel away sheath will be removed (Fig. 3, 4, 5, 6, 7).

The catheter will be connected to the port chamber. Using the same incision, a subcutaneous pocket will be prepared on the pectoral fascia. The port chamber will be fixed on the fascia of the pectoral muscle with three single non absorbable sutures. Flow for blood withdrawal and infusion is tested via cutaneous puncture (Huber needle). To complete the procedure the system is blocked with isotonic saline.

### Primary and secondary endpoints

#### Primary endpoint

The primary endpoint will be the primary success rate of the randomized implantation technique.

#### Definition of the primary endpoint

Primary success of the randomized implantation technique is defined as the correct position of the catheter checked introperatively by radiography and correct function checked by drawing blood and injecting isotonic saline fluid.

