### Analysis

Comparisons will be made of the primary endpoints of both intervention groups for all in the study included patients on an intention to treat basis. Furthermore there will be a second analysis on a "per protocol" basis including only patients who get strictly treated according to the study protocol. The outcome measures of the primary endpoint will be tested for significance with the chi square test.

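### The per-protocol rule can exclude patients because the allocated technique failed, and Table 1's analysed numbers conflict with intention to treat

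*Protocol article*

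**What the plan says.** All places are in the Protocol article.

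- **Analysis.** The primary endpoint is compared first by intention to treat in all included patients. A second, per-protocol analysis follows, "including only patients who get strictly treated according to the study protocol". The section does not say whether a patient in whom the allocated technique was attempted, failed and was replaced belongs to that set.
- **Study treatment.** The two procedures are described step by step. Neither description covers what follows if the catheter cannot be placed.
- **Table 1.** Each arm has 90 allocated, 10 who do not get the allocated procedure, and 80 analysed.
- **Primary endpoint** and **Definition of the primary endpoint.** "The primary endpoint will be the primary success rate of the randomized implantation technique". The criteria follow: "Primary success of the randomized implantation technique is defined as the correct position of the catheter checked introperatively by radiography and correct function", with function tested by drawing blood and injecting saline. Conversion is not mentioned.
- **Medical problem.** The conventional approach alone succeeded in 80%. The secondary puncture approach "achieves an overall success rate of 98"%.

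**The concern.** In this trial the main way to fail is that the allocated technique does not get the catheter into place, and a different route is then a foreseeable next step. Such a patient has left the procedure described for the arm and can be read as not strictly treated per protocol. Excluding that patient makes membership of the analysis set depend on the outcome being analysed. The arm with more failures loses more of them, so success rises in both arms, rises more in the weaker arm, and the difference shrinks. A supporting analysis built this way could appear to contradict a true difference found by intention to treat.

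Table 1 adds to the worry. It drops patients who did not get their allocated procedure from the analysed numbers, although the Analysis section names intention to treat first.

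A lesser point is that the two listed criteria, position and function, would both be met by a port placed through another route. The case report form is completed without blinding, so the coding of conversions should not be left to inference.

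**Working it through.** **Inputs**

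- Planning rates 0.80 (conventional) and 0.95 (modified), from Patients needed.
- Power statement: "there is a 80% chance that a trial involving 160 patients" "could detect a significant difference at a level of 5"%. Sidedness is not stated; two-sided is assumed.
- Test: "The outcome measures of the primary endpoint will be tested for significance with the chi square test".
- Table 1: 90 allocated, 10 not treated as allocated and 80 analysed per arm.
- g, the fraction of failures removed from an analysis set, and f, the fraction of failures rescued by another route and coded as success. Both are assumptions and are varied below.

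**Step 1: the plan's own figure**

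n per arm = [1.960·√(2·0.875·0.125) + 0.842·√(0.80·0.20 + 0.95·0.05)]² / 0.15² = (0.9167 + 0.3834)² / 0.0225 = 75.1, so 76 per arm or 152 in total.

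Power with 80 per arm = Φ[(0.15·√80 − 0.9167)/0.4555] = Φ(0.933) = 82.5%. Enumerating all possible tables gives 84.9% for the uncorrected chi-square, 76.8% with Yates correction and 79.3% for Fisher's exact test. The stated 160 patients and 80% power are therefore reasonable.

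Also, 160/(1 − 20/180) = 180. The 180 in Table 1 thus equals the 160 inflated for 20 patients not treated as allocated, and the 160 is what remains after removing them.

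**Step 2: removing failures**

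If a fraction g of failures is removed, p becomes p / [p + (1 − p)(1 − g)]. At g = 0.50 this is 0.80/(0.80 + 0.10) = 0.889 and 0.95/(0.95 + 0.025) = 0.974.

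| g | Conventional | Modified | Difference (points) | Power, 80 analysed per arm (normal approximation) |
|---|---|---|---|---|
| 0 | 80.0% | 95.0% | 15.0 | 82.5% |
| 0.25 | 84.2% | 96.2% | 12.0 | 73% |
| 0.50 | 88.9% | 97.4% | 8.5 | 57% |
| 0.75 | 94.1% | 98.7% | 4.6 | 34% |
| 0.90 | 97.6% | 99.5% | 1.9 | 17% |

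**Step 3: Table 1**

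Expected failures among 90 are 0.20·90 = 18 (conventional) and 0.05·90 = 4.5 (modified). If all 10 conventional patients removed were failures, success would move from 72/90 = 80% to 72/80 = 90%. The modified arm expects only 4.5 failures, so its 10 cannot all be failures at the planning rate. The article does not say who the 10 are.

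With all 90 per arm analysed and conversions counted as failures, the rates stay at 80% and 95%, and power = Φ[(0.15·√90 − 0.9167)/0.4555] = 86.7%.

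**Step 4: endpoint wording**

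If rescued placements were coded as successes, p becomes p + f(1 − p). Reading the 98% in Medical problem as final success after a second attempt gives f = (0.98 − 0.80)/0.20 = 0.90; that reading is an assumption. Enumerated uncorrected chi-square, 80 per arm:

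- f = 0: 80% against 95%, power about 85%.
- f = 0.50: 90% against 97.5%, about 49%.
- f = 0.90: 98% against 99.5%, about 5% (13% by normal approximation).

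**The case against.** The strongest reply is that the endpoint already excludes conversions. Its name and the opening of its definition tie success to the randomised technique, and position and function are only how that success is verified. The background separates the 80% single-technique rate from the 98% overall rate, and the sample size uses the 80%. This stands. A reader might infer from the two criteria that rescued ports count as primary successes, but the documents do not support that as the intended rule. The clause proposed for the definition is a clarification.

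Second, the per-protocol analysis comes second, and the intention-to-treat analysis as worded deletes nobody. This also stands: the Analysis section does not say that the main comparison loses failures. Only Table 1 raises that doubt, and it conflicts with the text. It is also true that an attempted but failed allocated procedure could be read as strict treatment. The rule permits the exclusion without stating it.

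Third, conversion coding and set membership often sit in the full protocol or analysis plan, and this is a condensed article. That explains missing detail. It does not cover a rule that is printed and, followed literally, selects on the outcome, or a printed flowchart that contradicts the printed analysis population.

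Fourth, extreme magnitudes are tempting. One might say power falls to about 3% because both arms would sit at 98%. That 3% is the rejection probability when the true rates are equal, so it is the size of the test and not power under the trial's alternative. Nor do the documents support removal of all 18 and 4.5 expected failures. Table 1 foresees equal numbers in both arms, which does not fit purely failure-driven removal.

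**Conclusion.** The per-protocol rule is badly fixed: on a literal reading it can exclude patients because of the primary outcome. The bias raises success in both arms and shrinks the difference. If half the failures are removed, 15 points become about 8.5. The range runs from 12.0 points at one quarter removed to 1.9 at nine tenths, and no conversion rate is given to narrow it. The effect falls on the supporting analysis. The first-named intention-to-treat analysis is unaffected as worded, but Table 1's 80 of 90 per arm contradicts it and must be reconciled.

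The endpoint definition needs only an explicit clause. The roughly 49% and 5% power figures show what a coding misreading would cost under assumed rescue fractions. They do not describe what the plan intends. The sample size is sound and needs no change.

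**What to change.** - **Analysis.** Add that a patient in whom the allocated technique was attempted and then converted stays in the per-protocol set and counts as a failure. Only departures unrelated to technique failure are excluded, such as an ineligible patient or the wrong technique used from the start.
- **Table 1.** Show 90 per arm analysed by intention to treat. If the per-protocol number is to appear, give it on a separate line and say who the 10 per arm are expected to be.
- **Definition of the primary endpoint.** As a clarification, add that placement by any technique or route other than the allocated one is not a primary success, even if final position and function are correct. Match the case report form item to this wording.

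The cost is a few sentences, one table edit and one form item, with no additional patients. The change concerns coding and analysis sets only and leaves clinical handling of a failed placement untouched.
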